### **8.3 Screening Log**

Participating study sites are required to document all screened candidates initially considered for inclusion in this study. If a subject is excluded from the study, the reasons for exclusion will be documented in the subject's source documents and on the screening log.

## **9 ENROLLMENT AND RANDOMIZATION PROCEDURES**

### **9.1 Enrollment Procedures**

Subjects will be enrolled at Day 0 (Visit 1/Week 0), after all baseline assessments have been completed. No subject may begin treatment prior to assignment of a unique subject identification number. Any subject identification numbers that are assigned will not be reused even if the subject does not receive treatment.

### **9.2 Randomization Procedures**

Subjects will be randomized after the Investigator has verified that they are eligible per criteria in Section 8.1 and Section 8.2. Randomization will be stratified by screening anti-CCP-2 status. Subjects will be randomized to receive placebo or BG9924 (1 of 5 dosing regimens) in a 2:2:2:2:1:1 ratio. Subjects withdrawn from the study may possibly be replaced.

Randomization will take place across all study sites using a centralized Interactive Voice Response System (IVRS; see Section 19.1.1). At randomization, the IVRS will assign a unique 6-digit subject identification number to each subject (the first segment of the number represents the study site and the second segment of the number represents the subject at that study site). The subject's identification number will be used on all of that subject's Case Report Forms (CRFs), test results, etc.

### **9.3 Blinding Procedures**

This is a randomized, multicenter, double-blinded, placebo-controlled study. The randomization will be computer generated and will be prepared by Biogen Idec by an unblinded statistician not involved with the operations of the study, prior to the start of the study. All study staff will be blinded to the subject treatment assignments, with the exception of the Pharmacist or designee, who is responsible for preparing the study treatment (BG9924 or placebo), and the Pharmacy Monitor. DMC members and the statistician providing data to the DMC will also be unblinded. To maintain the study blind, it is imperative that subject treatment assignments are not shared with the subjects, their families, or any member of the study team at the study site, Biogen Idec, [REDACTED]

---

CONFIDENTIAL

The information contained herein may not be used, disclosed, or published without the written consent of  
Biogen Idec Inc.

A matching placebo (0.9% Sodium Chloride for Injection) for BG9924 will be used in this study. The placebo is to be provided by the Investigational Sites. The precautions below are to be taken to ensure that blinding is adequately maintained throughout the study.

Dose-related effects of BG9924 on lymphocytes were noted in previous studies, so a potential exists for the Investigator to identify whether a subject is receiving BG9924 or placebo. To avoid compromising the blind, the sites will not receive the results of the lymphocyte counts from any visit after Screening, but will receive all other laboratory results.

To prevent potential blind breaks due to observed efficacy or laboratory changes, a “dual assessor” approach will be used to evaluate efficacy and safety. The Efficacy Assessor will only have access to the clinical efficacy data. The Safety Assessor will have access to both safety and efficacy data. This Investigator will make all treatment decisions based on the subject’s clinical response and laboratory parameters.

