## **12.3 BG9924 Concentration Assessments**

BG9924 concentrations will be measured to support the PK determinations in this study.

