### **13.2 Laboratory Safety Assessments**

The following laboratory tests will be performed by the central laboratory to assess the safety profile of BG9924:

- International normalized ratio (for anticoagulant monitoring [INR]), prothrombin time (PT), and activated partial thromboplastin time (aPTT)
- Urinalysis (protein, glucose, ketones, occult blood, and WBCs by dipstick and microscopic examination, if indicated)
- Blood chemistry (AST, ALT, alkaline phosphatase, total protein, albumin, cholesterol, total bilirubin, blood urea nitrogen, uric acid, creatinine, lactate dehydrogenase [LDH], potassium, sodium, chloride, calcium, phosphorous, bicarbonate, and glucose)
- Hematology (hemoglobin, hematocrit, red blood cell [RBC] count, WBC count [absolute and differential counts], and platelet count)
- ANA and anti-dsDNA antibody assays
- Quantitative Ig (total, IgA, IgG, and IgM)
- Serum anti-BG9924 antibody assay
- Leukocyte subset analysis: CD3+, CD4+, CD8+, CD19+, CD16+, CD56+, and CD14+

To preserve the study blind, lymphocyte counts will not be sent to the investigational sites.

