#### **14.2.4 Visit 2 (Week 1, Day 7 $\pm$ 2)**

- Vital signs: temperature, heart rate, respiratory rate, and supine blood pressure (after 5 minutes' rest)
- Blood samples collected for serum BG9924 PK concentration
- Study treatment administration

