#### **19.1.4 Central Laboratories for Laboratory Assessments**

ESR will be analyzed by a local laboratory.

[REDACTED] has been selected as the central laboratory to perform the following assessments:

- hsCRP assay
- RF
- Anti-CCP-2 antibody
- Hematology
- Blood chemistry
- Urinalysis
- Serum pregnancy
- Quantitative Ig
- INR, PT, and aPTT
- HCV, HBsAg, HBsAb, and HBcAb
- ANA
- Anti-dsDNA antibody
- Tetanus antibody titers

The following assessments will be performed by Biogen Idec or a specialized laboratory selected by Biogen Idec:

- Serum BAFF
- COMP
- Calgranulin
- MMP3
- Cytokines
- Quantitative FACS (specialized laboratory)
- Serum anti-BG9924 antibody (specialized laboratory)
- Serum PK drug concentrations (specialized laboratory)
- RNA analysis

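### Sections 9.3 and 13.2 withhold only lymphocyte counts, so read literally they also send sites anti-BG9924 antibody results and, through the word 'all', serum BG9924 concentrations

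*Protocol*

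**What the plan says.** Section 9.3 (Blinding Procedures) keeps all study staff blinded except the pharmacist or designee and the pharmacy monitor; DMC members and the statistician who serves them are also unblinded. It explains that earlier studies showed dose-related effects on lymphocytes that could let an Investigator recognise active drug. To prevent this, it states that "the sites will not receive the results of the lymphocyte counts from any visit after Screening, but will receive all other laboratory results".

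Section 13.2 opens with "The following laboratory tests will be performed by the central laboratory to assess the safety profile of BG9924". Its list includes "Serum anti-BG9924 antibody assay", and it ends with "To preserve the study blind, lymphocyte counts will not be sent to the investigational sites".

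Section 12.3 says of drug levels only that "BG9924 concentrations will be measured to support the PK determinations in this study". Section 19.1.4 puts both the anti-BG9924 antibody and the serum drug concentrations among the assays run by the sponsor or a specialized laboratory. Neither section says to whom results are reported.

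Sections 9.3 and 12.1 add a dual-assessor arrangement. The Efficacy Assessor sees clinical efficacy data only. The Safety Assessor sees safety and efficacy data, reviews laboratory results and makes all treatment decisions.

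**The concern.** The rule is closed: it names one withheld item and releases the rest. The item it names is an indirect pharmacodynamic signal. Two results that the protocol also collects are more direct. The comparator is saline (Section 10.2), so a measurable BG9924 concentration identifies active treatment. An anti-BG9924 antibody that turns positive after baseline suggests it. A laboratory or site that follows the sentence as worded would release the stronger signals and mask the weaker one, which defeats the purpose of the section in which the sentence stands.

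If the Safety Assessor learned or suspected the arm, two things could be affected. One is the decision to add or increase a DMARD before Week 14, which Section 11.4.2 treats as rescue and scores as treatment failure. The other is the relatedness rating of adverse events (Sections 15.2 and 15.3.1).

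**Working it through.** The protocol gives no figure to reproduce, so the check sets its sections side by side and counts the affected samples.

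**Step 1. Is either assay covered by the rule, and is either exempt?**

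| Result | Listed as a laboratory safety test (13.2)? | Laboratory | Reporting to sites restricted anywhere? |
|---|---|---|---|
| Lymphocyte counts | Part of hematology and the subset analysis | Central (13.2) | Yes, after Screening (9.3); also 13.2 |
| Anti-BG9924 antibody | Yes | Central (13.2), specialized (19.1.4) | No |
| Serum BG9924 concentration | No; own section (12.3) | Specialized (19.1.4) | No |

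The antibody assay is inside the very list that the Section 13.2 masking sentence follows, and that sentence does not name it. The concentrations are outside that list. They fall under the rule only because Section 9.3 says 'all other'. The visit schedules (Section 14.2) and the unblinding procedures (Section 15.5.3) contain no exemption for either.

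**Step 2. How many results are involved before the endpoint?** The endpoint visit is Visit 9 (Week 14).

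- Concentrations: from Visit 2 ("Blood samples collected for serum BG9924 PK concentration") the sample is drawn in all subjects at Weeks 1, 2, 4, 6, 8, 10 and 12. That is 7 samples after the first dose and before Week 14.
- Antibody: Weeks 0, 6, 14 and 26. Only Week 6 lies after the first dose and before Week 14, so 1 sample.
- The Week 14 samples of both assays are drawn at the endpoint visit and cannot affect the Week 14 outcome through earlier decisions.

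The level of a concentration would also carry some information on dose: the every-other-week regimens run from 5 mg to 200 mg, a ratio of 200 / 5 = 40.

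**Step 3. Who is exposed?** The Efficacy Assessor does the joint counts and the Investigator's global assessment and does not see laboratory data. Subject and efficacy assessments are to precede the safety assessments where possible (Sections 12.1 and 14.2). The Safety Assessor is not shielded.

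**Step 4. How could that reach ACR50?**

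- Rescue up to Week 14 counts as treatment failure (Section 11.4.2) and as non-response from then on (Section 16.2).
- Withdrawal is not itself scored as failure. Section 16.2 scores missing measurements as failure, and subjects who withdraw early are asked to complete the Week 14 evaluations (Sections 11.2.2 and 14.2.13). A withdrawal therefore matters only if it leaves Week 14 data missing.

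**The case against.** The strongest reply is that nobody would read the sentence this way. It is presented as a precaution to protect the blind, in a section that insists assignments not be shared. The natural contrast is between lymphocyte counts and the other routine central-laboratory results. No section positively says that concentrations or antibodies are reported to sites. Concentrations have their own section with a stated PK purpose and go to a different laboratory.

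Much of this stands for the concentrations, where the case rests on one word. It stands less well for the antibody, which Section 13.2 places among the central-laboratory safety tests. Assigning an assay to a specialized laboratory does not restrict its reporting. Nor can delayed batch analysis be assumed: Sections 12.2, 12.4 and 12.5 mention long storage for disease markers, cytokines and RNA, while Sections 12.3 and 13.2 say nothing of the kind for these two assays.

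A second reply is that the dual-assessor arrangement already protects the endpoint. It does protect the joint counts, both of which must improve by 50% for ACR50, and the Investigator's global assessment. It does not cover treatment decisions or causality ratings.

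A reader might go further and infer that sites would in fact be unblinded, or that the type I error is raised by a definite amount. The documents support neither. How many subjects could be recognised in time depends on antibody incidence, assay sensitivity and reporting time, none of which is given. Any error-rate figure would need an assumed bias. Moreover, scoring rescue as failure can only remove responders: a false advantage would require sparing active-arm subjects from rescue who then meet ACR50, or extra rescue of placebo responders. Nothing in the protocol sizes either.

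**Conclusion.** The point holds as a defect in a stated rule. Followed literally, Sections 9.3 and 13.2 release anti-BG9924 antibody results and, through the word 'all', serum BG9924 concentrations. This conflicts with the blinding requirement in Section 9.3. The antibody is the firmer half.

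The extent is one on-treatment antibody result and seven concentration results per subject before the Week 14 visit. The exposure is confined to the Safety Assessor's decisions, other site staff and causality ratings. The conclusion assumes that sites and laboratories apply the text as written; if the sponsor meant only routine safety reports, the wording still needs to say so. The protocol does not show that unblinding would occur, and the size of any bias cannot be derived from it. The correction is worth making because the conflict concerns the double blind itself and is cheap to remove.

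**What to change.** In Sections 9.3 and 13.2, replace the open release of all other results with an explicit rule. Serum BG9924 concentrations and anti-BG9924 antibody results, together with the lymphocyte data, are withheld from sites and from blinded sponsor staff until unblinding; the remaining safety laboratory results are sent. State that the withheld results remain available to the DMC, which already reviews unblinded safety data (Section 19.2.1). Reconcile Sections 13.2 and 19.1.4 on whether the central or a specialized laboratory runs the antibody assay.

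The cost is a change to the laboratory reporting set-up, and that sites do not see the antibody result during the study. That second cost is not nil: Section 13.2 classes the assay as a safety test, and Section 9.3 bases treatment decisions on laboratory parameters in general. No section, however, makes a subject-care decision depend specifically on the antibody result.

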## 10 STUDY TREATMENT DESCRIPTION AND ALLOCATION

Study treatment must be stored in a secure location. Accountability for study treatment is the responsibility of the Investigator. More details concerning this responsibility are included in Section 10.4.

Study treatment must only be dispensed by a Pharmacist or medically qualified staff. Study treatment is to be dispensed only to subjects enrolled in this study. Once study treatment is prepared for a subject, it can only be administered to that subject. Study treatment vials are for *one-time use only*; any study treatment remaining in the vial should not be used for another subject.

Study site staff should refer to the Directions for Handling and Administration (DHA) located in the Pharmacy Manual and the Study Reference Guide for specific instructions on the handling and administration of the study treatment. Any changes to the DHA will be communicated to the study sites by updates to the DHA document and would supersede instructions provided in this protocol and all other references (e.g., Investigator Brochure).

### 10.1 BG9924

[figure not shown]

---

CONFIDENTIAL

The information contained herein may not be used, disclosed, or published without the written consent of  
Biogen Idec Inc.

## 10.2 Comparator

The placebo (control agent) to be used in this study will be sterile normal saline (0.9% Sodium Chloride for Injection). Sterile normal saline will be supplied by the investigational site. The manufacturer's directions for material storage and handling are to be followed, as are standard clinical practices for ensuring sterility of the material.

## 10.3 Additional Protocol-Designated Products

### *Methotrexate*

Subjects must continue on MTX ( $\geq 10$  mg/week to  $\leq 25$  mg/week) through Week 14 of the study (primary endpoint analysis), as prescribed by their rheumatologist or general care physician. The MTX treatment regimen should remain stable and the route of administration should not be changed through Week 14 (and through Week 26 if possible). The dose may be decreased if required due to toxicity. The dose should not be increased prior to Week 14.

### *Oral Folate*

All subjects must agree to take oral folate ( $\geq 5$  mg/week) for the duration of the study (as per the inclusion criteria) to counter the inhibitory effect of MTX on the folic acid metabolic pathway.

## 10.4 Study Treatment Accountability

The study site must maintain accurate records demonstrating dates and amount of study treatment received, to whom dispensed (subject-by-subject accounting), and accounts of any study treatment accidentally or deliberately destroyed.

Unless otherwise notified, all vials both used and unused, must be saved for study treatment accountability. At the end of the study, reconciliation must be made between the amount of study treatment supplied, dispensed, and subsequently returned to Biogen Idec. A written explanation will be provided for any discrepancies.

After all investigational drug is accounted for, the Investigator must return all unused vials of study treatment as instructed by Biogen Idec, unless permission is granted by Biogen Idec to destroy drug on site.

If any study treatment supplies are to be destroyed at the site, the institution/Principal Investigator(s) must obtain prior approval by Biogen Idec. After such destruction, the institution/Principal Investigator(s) must notify Biogen Idec, in writing, of the method of destruction, the date of destruction, and the location of destruction.

## 11 TREATMENT

### 11.1 Treatment Schedule

Subjects will receive BG9924 or placebo via SC injection by a healthcare provider at the study site every other week for 12 weeks. All subjects will receive a loading dose as described below. Subjects will be randomized to one of the following dose groups:

- Placebo every other week (loading dose at Weeks 0 and 1)
- BG9924 5 mg every other week (loading dose of 3 mg at Weeks 0 and 1)
- BG9924 70 mg every other week (loading dose of 40 mg at Weeks 0 and 1)
- BG9924 200 mg every other week (loading dose of 120 mg at Weeks 0 and 1)
- BG9924 70 mg monthly (alternates with placebo every other visit, loading dose of 40 mg at Weeks 0 and 2)
- BG9924 200 mg monthly (alternates with placebo every other visit, loading dose of 120 mg at Weeks 0 and 2)

### 11.2 Removal of Subjects from Treatment and/or Study

#### 11.2.1 Discontinuation of Treatment

Unless otherwise indicated, a subject *must* permanently discontinue BG9924 for any of the following reasons:

- Occurrence of severe (in the opinion of the Investigator) local injection site reaction or hypersensitivity reaction.
- Occurrence of any clinically significant (in the opinion of the Investigator) opportunistic infection or other serious infection.
- Occurrence of any non-cutaneous malignancies or melanoma.
- The subject becomes pregnant. Treatment must be discontinued *immediately*. Report the pregnancy according to the instructions in Section 15.5.2.
- The subject desires to discontinue study treatment under this protocol.
- The subject experiences a medical emergency that necessitates permanent discontinuation of treatment.
- The subject experiences a medical emergency that necessitates unblinding of the subject's treatment assignment.
- The Investigator determines discontinuing the study treatment is in the best interest of the subject.

Subjects who prematurely discontinue treatment will be permanently withdrawn from treatment, and every effort must be made to encourage them to complete all follow-up

visits from Visit 9/Week 14 to Visit 12/Week 26. Subjects who prematurely discontinue may possibly be replaced in the accrual scheme. The reason(s) for discontinuation of the study treatment must be recorded in the subject's CRF.

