| Monitoring of adverse events                     | MONITOR AND RECORD THROUGHOUT THE STUDY AS PER INSTRUCTIONS IN SECTION 15.2 |                                       |                                                   |
| Monitoring of concomitant therapy                | MONITOR AND RECORD THROUGHOUT THE STUDY AS PER INSTRUCTIONS IN SECTION 15.2 |                                       |                                                   |

CONFIDENTIAL

The information contained herein may not be used, disclosed, or published without the written consent of Biogen Idec Inc.

Vital signs include temperature, heart rate, respiratory rate, and blood pressure. Blood pressure to be performed supine after 5 minutes rest.

Measurements include: swollen and tender joint counts (66/68), subject/Investigator global assessment of disease activity, HAQ-DI, and subject's assessment of pain (VAS)

Assessments include: subject-reported dryness including VAS (ocular, vaginal, skin, and oral) and OSDI. To be conducted in subjects with Sjogrens syndrome only.

ESR to be performed at local laboratory.

RA disease markers include: serum BAFF, COMP, calgranulin, and MMP3.

**Only to be taken from subjects participating in the optional PK sub-study.**

PPD test to be read 48-72 hours after planting.

Not required if performed within 3 months prior to Day 0 and was without clinically significant abnormality. However, if PPD induration is  $\geq 5$  mm, but  $< 10$  mm (size of raised bump, not redness), a chest X-ray is required, regardless of when the last X-ray was taken.

Only to be taken from subjects with positive ANA/anti-dsDNA at Week 14.

a**Visit only applicable to subjects participating in the optional PK sub-study. Subjects will sign a separate informed consent form.**

bOption to enter safety data extension study. If subject withdraws from the study prior to Visit 9/Week 14, all Week 14 assessments should be completed at the withdrawal visit.

cIf subject withdraws from the study during the post-treatment period, Week 26 assessments should be completed at the withdrawal visit.

---

CONFIDENTIAL

The information contained herein may not be used, disclosed, or published without the written consent of  
Biogen Idec Inc.

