#### 15.5.3.1 Accidental Unblinding

If a subject's treatment assignment is unblinded, the subject must immediately discontinue study treatment. The subject should remain in the study and complete the study-specific follow-up tests and assessments (Week 14 to Week 26).

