#### **16.2.6.2 Methods of Analysis**

The proportion of subjects who developed anti-BG9924 antibodies will be summarized.

The relationship between the antibody response and selected efficacy and safety data will be explored.

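### Sections 11.2.1 and 15.5.3.1 name only the Week 14 to Week 26 visits for subjects who stop treatment but stay in the study, leaving up to 14 weeks without a scheduled visit or sample

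*Protocol*

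**What the plan says.** Section 11.2.1 lists the reasons for permanent discontinuation of treatment. They include a reaction criterion ("Occurrence of severe (in the opinion of the Investigator) local injection site reaction or hypersensitivity reaction"), an infection criterion ("Occurrence of any clinically significant (in the opinion of the Investigator) opportunistic infection or other serious infection") and a malignancy criterion ("Occurrence of any non-cutaneous malignancies or melanoma"). For subjects who stop, it then says: "Subjects who prematurely discontinue treatment will be permanently withdrawn from treatment, and every effort must be made to encourage them to complete all follow-up". The same sentence goes on to give the range: "visits from Visit 9/Week 14 to Visit 12/Week 26".

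Section 15.5.3.1 requires a subject whose assignment is unblinded to stop treatment and adds: "The subject should remain in the study and complete the study-specific follow-up tests and assessments (Week 14 to Week 26").

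Three other places bear on the same subjects:

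- Section 7.2 (Treatment Period) tells eligible subjects to attend according to the visit table in Section 4 and the schedule in Section 14. It makes no exception for subjects who are off treatment.
- Footnote b of the Section 4 table sets an early assessment, but for study withdrawal: "If subject withdraws from the study prior to Visit 9/Week 14, all Week 14 assessments should be completed at the withdrawal visit". Section 11.2.2 asks for the same, as encouragement and where possible.
- Section 14.2.13 assigns the Visit 9 evaluations to subjects who complete the treatment period or withdraw from the study before Week 14. Subjects who stop treatment and stay are not named.

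**The concern.** Two sections, written for exactly this group, name a visit range that starts at Week 14. No section sets a visit at the time treatment stops. The early battery depends on leaving the study, so on paper a subject who stays in can have fewer data planned near the event than one who leaves.

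The subjects concerned include those stopped for serious infection, hypersensitivity or malignancy, whose course after exposure is among the most informative in a dose-finding study. Four uses of the data are exposed:

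- **Safety laboratory data.** Recovery of blood counts and chemistry after stopping is not sampled on schedule. The Data Monitoring Committee's quarterly safety review (Section 19.2.1) would have no scheduled laboratory value for such a subject during the gap.
- **Immunogenicity.** Section 16.2.6.2 plans that "The relationship between the antibody response and selected efficacy and safety data will be explored". Section 16.2.6.1 requires at least one post-baseline assessment. A subject stopped for hypersensitivity before Week 6 who does not return at Week 14 or later contributes no post-baseline antibody sample.
- **Pharmacokinetics.** Serum concentration is drawn at every regular treatment-period visit. Concentrations after stopping would be lost, although Section 16.2.2.2 intends to study factors that affect disposition, including anti-drug antibodies.
- **Continuous efficacy endpoints.** Section 16.2 fills missing values by last observation carried forward. With fewer interim assessments, an older value is carried.

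**Working it through.** The protocol states no figure for this gap. The check is a count from the Section 4 table and the visit days in Section 14.2.

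**Inputs**

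- Regular visit days: Visit 1 = 0, Visit 2 = 7, Visit 3 = 14, Visit 4 = 28, Visit 5 = 42, Visit 6 = 56, Visit 7 = 70, Visit 8 = 84, Visit 9 = 98.
- ACR core set, hsCRP/ESR, hematology and chemistry: Days 0, 14, 28, 42, 70, 98.
- Anti-BG9924 antibody and quantitative immunoglobulins: Days 0, 42, 98.
- Vital signs and serum PK: every regular visit.

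**Formula.** If d is the day of the last attended visit, the gap in weeks is (98 − d)/7. Assessments passed over are those scheduled strictly between day d and Day 98.

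| Last visit attended | Gap, weeks | Regular visits passed over (each with vital signs and PK) | ACR core sets, and as many hematology/chemistry draws | Antibody/Ig sampling times |
|---|---|---|---|---|
| Visit 1, Day 0 | 98/7 = 14 | 7 | 4 (Weeks 2, 4, 6, 10) | 1 (Week 6) |
| Visit 2, Day 7 | 91/7 = 13 | 6 | 4 | 1 |
| Visit 3, Day 14 | 84/7 = 12 | 5 | 3 | 1 |
| Visit 4, Day 28 | 70/7 = 10 | 4 | 2 | 1 |
| Visit 5, Day 42 | 56/7 = 8 | 3 | 1 | 0 |
| Visit 6, Day 56 | 42/7 = 6 | 2 | 1 | 0 |
| Visit 7, Day 70 | 28/7 = 4 | 1 | 0 | 0 |
| Visit 8, Day 84 | 14/7 = 2 | 0 | 0 | 0 |

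With the 3-day window at Visit 9, the longest gap is 101/7 = 14.4 weeks.

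**Comparison with a subject on schedule.** The longest planned interval between Day 0 and Day 98 is 2 weeks for visits, 4 weeks for ACR and laboratory assessments, and 8 weeks for antibodies. After a Day 0 stop, all three become 14 weeks.

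**Effect on carried-forward values.** Take a subject who stops after Week 2 and then misses Week 14. The last available DAS28 or HAQ-DI is from Week 2. Had the remaining visits been attended, it could be from Week 10. SF-36 and FACIT-F are collected up to Week 14 only at Visits 1 and 9, so the gap does not change them.

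**Does Section 7.2 close the gap?** It gives a general attendance rule for the treatment period. Sections 11.2.1 and 15.5.3.1 are the specific rules for subjects who have stopped, and both name a range that begins at Week 14. The general rule does not clearly override them, and Section 14.2.13 does not settle the matter because it omits this group.

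**The case against.** The best defence is that nothing expressly cancels Visits 2 to 8. Section 11.2.1 can be read as securing post-treatment follow-up on top of attendance already owed under Section 7.2. That reading is possible, but it is the weaker one, since Section 15.5.3.1 gives the same range as what the subject should complete. Even if it were right, sites could reasonably act on either reading, and that needs correcting.

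Other points in the plan's favour stand and limit the concern:

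- A reader might infer that these subjects have no safety follow-up. The protocol does not support that. Section 15.2 continues event recording to the end-of-study visit, and Section 15.6 requires active pursuit of information on serious events. What is missing is protocol-timed visits, vital signs and samples.
- A reader might infer that the primary endpoint is lost. It is not: Week 14 is the first visit these subjects are asked to attend. That a long gap makes a missed Week 14 visit more likely is plausible, but no figure in the protocol supports it.
- A reader might infer that a withdrawing subject always gets the full battery. Section 11.2.2 only encourages it.
- A reader might apply the 15% dropout of Section 16.4 to count affected subjects. That rate is a power-calculation allowance for dropout, not a rate of stopping treatment while remaining in the study. The protocol gives no rate for this group.
- The antibody loss is one sampling time, only for stops before Week 6. The analysis it feeds is exploratory, and Weeks 14 and 26 remain on the schedule.

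**Conclusion.** The concern holds as a gap in planned data collection and as a set of passages that need reconciling. On the literal reading of Sections 11.2.1 and 15.5.3.1, a subject who stops treatment but stays in the study has no scheduled visit, vital-sign, laboratory, PK or antibody assessment until Day 98. The gap is 14 weeks at most, 12 weeks after a Week 2 stop, and 2 weeks (the normal interval) after a Week 12 stop.

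The loss is of interim safety, PK, antibody and efficacy data, including values that would otherwise be carried forward. It is not a loss of adverse event reporting or of the planned Week 14 ACR50 assessment. The gap lengths rest on the visit table and on sites following the specific sections over the general rule in Section 7.2. How many subjects are affected cannot be determined from the protocol. An analysis plan could not repair this later, because samples that were never drawn cannot be recovered. The change is cheap and worth making.

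**What to change.** Reconcile Sections 7.2, 11.2.1, 14.2.13 and 15.5.3.1 and footnote b of the Section 4 table, so that all say the same about subjects who stop treatment but remain in the study. State that these subjects are encouraged, with the same effort Section 11.2.1 already asks of sites, to attend all remaining scheduled visits through Visit 12 at their planned times, without injection, and to have the assessments already listed for those visits. Name this group in Section 14.2.13 among those who have Visit 9 evaluations.

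Attendance stays a matter of encouragement, which matters because one listed reason for stopping is the subject's own wish. No draws are added beyond the existing schedule. Stopping criteria and clinical care are unchanged.

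The cost is an amendment to the wording, the usual per-visit expense, and visit burden for subjects no longer receiving study drug.
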